### Assessment of eligibility and outcome measures

The time schedule of enrolment, interventions and assessments for participants can be seen in Fig. 1. At the point of referral, basic information pertaining to the inclusion and exclusion criteria was sought from the clinical team, this included information relating to clozapine use, diagnosis, age, developmental disability, language and current/previous receipt of CBT. Research assistants (RA) met with potential participants before the first assessment to explain the trial, discuss the participant information sheet and provide an opportunity for the potential participant to ask questions. After this, the RA sought written informed consent from those who wish to take part in the trial. Eligibility on the PANSS was determined at the baseline assessment.

**Fig. 1 Fig1:**
[figure not shown]
Trial flow diagram

The primary outcome measure is the total PANSS score at 21-month assessment (12 months’ follow-up from the end of treatment). The primary outcome will allow for comparison with other published trials, inclusion of our results in any future systematic reviews and meta-analyses. Having the primary outcome at 12-month follow-up will allow an evaluation of the benefits of CBTp beyond the end of treatment. The PANSS is a 30-item rating scale designed to provide a comprehensive assessment of psychopathology in adult patients with schizophrenia. Five components have been reported: positive, negative, depression-anxiety, agitation-excitement, and disorganisation [35, 36]. The PANSS was completed at baseline assessment, 9-month follow-up and 21-month follow-up.

In addition to the PANSS, we administered a number of other measures at baseline assessment. The Psychotic Symptom Rating Scales (PSYRATS) [37] was used to assess dimensions of auditory hallucinations and delusional beliefs including frequency, preoccupation, location, loudness, conviction, and amount of unpleasant content, severity of unpleasant content, amount of distress, intensity of distress, degree and impairment of control. Personal and social occupational functioning was assessed by the Personal and Social Performance Scale (PSP) [38], this provided an assessment of functioning in four areas (socially useful activities, personal and social relationships, self-care and aggressive behaviours). Depression was assessed using the Calgary Depression Rating Scale for Schizophrenia (CDSS) [39]. Global illness severity was assessed using the Clinical Global Impression Scale (CGI) [40] and in addition to the clinician version a participant version (CGI-P) was utilised to obtain the participants perception of the severity of their mental health difficulties. Working memory was assessed using the Working Memory Letter Number (LN) span [41]. Furthermore, the participants were asked to complete a number of self-report questionnaires. These include: meta-worry subscale of the Anxious Thoughts Inventory (ATI [42]), The Process of Recovery Questionnaire (QPR [43]), the Alcohol Use Disorder Test (AUDIT [44]) and the Drug Abuse Screening Test (DAST [45]). Several self-report psychological measures were used to identify mechanisms of change and predictors of outcome these include the Interpretation of Voices Inventory, (IVI [46]) as a measure of appraisals of voices; the Beliefs About Paranoia Scale (BAPS [47]) as a measure of appraisals of paranoia; the Psychosis Attachment measure (PAM [48]) as a measure of attachment style; the Brief Core Schema Scale (BCSS [49]) as an measure of positive and negative beliefs about others; the Internalised Stigma Scale (ISMI [50]) and the Common Responses Questionnaire, which is a measure of common responses to psychotic experiences.

Following the baseline assessment, we invited all participants to attend two face-to-face assessments at 9 months (end of treatment) and 21 months (12-month follow-up). All of the measures detailed above are completed at the 9-month assessment with the addition of the Childhood Trauma Questionnaire (CTQ [51]), which is used to retrospectively assess histories of abuse and neglect. All of the measures listed above are also completed at 21-month follow-up with the exception of the Working Memory Letter Number (LN) and the CTQ. We also ask all participants at the 21-month follow-up to complete a self-report measure of potential adverse effects from trial involvement. This measure was developed specifically for use in the FOCUS trial to measure these broad categories: worsening difficulties; poor engagement (including low motivation); situational change; not getting benefit; stigma; increased conflict with others (care team, family etc.) and feeling better.

The Economic Patient Questionnaire (EPQ [32]) at baseline, 3, 6, 9, 13, 17 and 21 months is used to collect data from participants about the range and frequency of health and social care services used. The EPQ is used to identify hospital care and details of this are collected from case notes. The EPQ is administered by telephone at the 3, 6, 13 and 17 months’ follow-up. The Euroqol (EQ-5D) is a generic and validated health status questionnaire, shown to have acceptable validity in people with schizophrenia in European countries [52] and used in previous trials of interventions for people with schizophrenia [32, 53]. It was administered at baseline, 9 and 21 months’ follow-up. Quality adjusted life years (QALYs) gained from baseline to end of scheduled follow-up will be estimated as the number of weeks multiplied by the utility of observed survival. The utility values will be estimated from the Euroqol EQ-5D health status questionnaire completed at each follow-up assessment and the associated published societal utility tariffs.

Participants are offered choice regarding the duration of the of assessments visit, including the option of breaks and multiple assessment sessions. Assessment measures are clearly prioritised so that the most important are collected first to avoid missing data. We have a standard protocol for managing any distress that is associated with the completion of measures, which has been developed in collaboration with service users; this includes the offer of telephone contact within 48 h of assessments in order to check on participant well-being.

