**Discussion:**

The recruitment target of 485 was achieved, with a final recruitment total of 487. This trial is the largest definitive, pragmatic clinical and cost-effectiveness trial of cognitive behavioural therapy for people with schizophrenia whose symptoms have failed to show an adequate response to clozapine treatment. Using a prognostic risk model, baseline information will be used to explore whether there are identifiable subgroups for which the treatment effect is greatest.

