### Interventions

Cognitive Behavioural Therapy for psychosis (CBTp) is delivered by appropriately qualified psychological therapists (clinical psychologists, counselling psychologists or other mental health professionals with specialist training in CBT). CBTp is delivered on an individual basis over a period of 9 months and includes up to 30 treatment sessions on an approximately weekly basis over the 9-month treatment window. CBTp is based on a specific cognitive model [11], since there is good evidence that CBTp based on empirically validated models is far superior to more eclectic cognitive behavioural approaches [29]. CBTp is based on a manualised approach in which, the assessment allows the development of an individualised formulation based on the cognitive model. The specific interventions are dependent on the individual formulation, but the range of permissible interventions is described in our published manuals [12, 30]. The aims of CBTp are to reduce distress (particularly that associated with psychotic symptoms) and improve quality of life. It is a collaborative therapy that works with the problems and goals that are agreed between patient and therapist. Thus, treatment targets often include positive symptoms, but frequently also include social issues such as improving relationships or developing meaningful social roles and issues of comorbidity including anxiety and depression. If comorbidity includes problematic drug or alcohol use, this can also be prioritised. Fidelity to the treatment protocol is ensured by weekly supervision of the therapists and assessed by rating audio recordings of therapy sessions using the Cognitive Therapy Scale-Revised [31]. All therapists in participating centres received initial training, which consisted of a residential week that covered assessment and formulation based on a specific cognitive model [11], milestones and assumptions for the therapy process and change strategies. Therapy supervision is provided by means of weekly face to face or telephone meetings. All CBTp sessions are audio recorded with the patient’s consent (patients may be asked to listen to the tapes as part of their homework) and a sample of tapes are rated using the CTSR in order to monitor fidelity and assist supervision; this is done throughout the lifetime of the trial in order to provide quality assurance and ensure corrective action can be taken if required. Following each session, therapists complete a session record that monitors the content of the session in terms of agenda targets, homework tasks and change strategies used. Thus, fidelity can be used as a mediating variable in supporting analyses. Additionally, this data is used throughout the trial to monitor adherence and address any adherence difficulties with therapist training sessions. The session records are anonymised and stored electronically in a database that is only accessible to specific members of staff who have been granted the necessary privileges. We would consider discontinuing therapy at the participants request to do so.

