### Statistical analysis

Statistical analysis will take place after full recruitment and follow-up (i.e. there will be no interim analyses for efficacy, although an independent Data Monitoring Committee monitors trial progress and specifically any safety issues on a regular basis). The results of the trial will be presented following the standard CONSORT recommendations. Baseline and follow-up data will be summarised using the appropriate descriptive statistics and graphical summaries. Treatment effects will be presented with 95 % confidence intervals (CI). There will be no adjustment to secondary outcomes CIs for multiple testing. The primary outcome (PANSS total score at 21 months) will be analysed using a linear model that adjusts for pre-specified baseline covariates (baseline PANSS, sex, age) and includes a random effect for site. The development of treatment effects over time will be explored using a repeated measures mixed effects model that makes use of all available data, this assumes missing at random conditional on the observed covariates. The primary analysis will be intention-to-treat on available data (i.e. analyse as randomised). Secondary outcomes will be analysed in a similar way with generalised linear models appropriate for the distribution of the outcome.

We will try to identify subgroups for which the treatment effect is greatest using a prognostic risk model using baseline information. Response to treatment as measured by change in PANSS from baseline to 21 months will be explored in a general linear model. Covariates will include age; sex; baseline secondary outcome measures; childhood trauma; beliefs about self and others; working memory performance; and treatment allocated. Outcome analyses will be repeated excluding participants where the blind was broken to determine the robustness of the findings.

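### The exploratory predictor model is presented as using baseline information, but its childhood trauma covariate is measured only at the 9-month, end-of-treatment visit

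*Protocol article*

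**What the plan says.** The Statistical analysis section sets the aim: "We will try to identify subgroups for which the treatment effect is greatest using a prognostic risk model using baseline information". The Discussion paragraph of the abstract says the same: "baseline information will be used to explore whether there are identifiable subgroups for which the treatment effect is greatest". The Background also gives the model's purpose as finding baseline factors that predict a good response to CBTp.

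The response modelled is change in PANSS from baseline to 21 months, and the covariates are listed: "Covariates will include age; sex; baseline secondary outcome measures; childhood trauma; beliefs about self and others; working memory performance; and treatment allocated".

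The timing of measures is given under Assessment of eligibility and outcome measures. The baseline battery is listed instrument by instrument, and the CTQ is not among them. It first appears after baseline: "All of the measures detailed above are completed at the 9-month assessment with the addition of the Childhood Trauma Questionnaire", described as a measure "which is used to retrospectively assess histories of abuse and neglect". The measures repeated at 21 months are all those listed "with the exception of the Working Memory Letter Number (LN) and the CTQ". The 9-month visit is labelled as the end of treatment, and the Interventions section states that "CBTp is delivered on an individual basis over a period of 9 months".

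**The concern.** A predictor of treatment response should be fixed before treatment can touch it. Here one covariate in a model presented as baseline-only is recorded after one arm has had up to 30 sessions of individual, formulation-based therapy and while participants know their allocation. Two things follow.

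First, the recorded score is a retrospective account. What is recalled or disclosed, or the symptom state in which the questions are answered, could differ by arm. Adjusting for such a score, or reading it as a treatment modifier, is then not the same as using a baseline trait.

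Second, a score exists only for people assessed at 9 months, so attendance after randomisation decides who can enter a joint complete-case model. Attenders may lack it too, because the section on change of status offers unsure participants a reduced set of measures.

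At stake is the interpretation of the predictor analysis, which the article's main Discussion section says should help patients and clinicians decide about accessing CBTp. The estimate of the primary treatment effect is not at stake.

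**Working it through.** **1. Timing against model, covariate by covariate**

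| Covariate in the model | When collected |
|---|---|
| Age, sex | Baseline characteristics; also covariates of the primary model |
| Baseline secondary outcome measures | Baseline, by name |
| Beliefs about self and others (Brief Core Schema Scale) | Baseline battery |
| Working memory (Letter Number span) | Baseline battery, repeated at 9 months |
| Treatment allocated | Randomisation |
| Childhood trauma (CTQ) | 9 months only |

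Childhood trauma is the single exception. No other trauma instrument is described, and no sentence reconciles the timing with the baseline description.

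**2. Who would have a score**

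Inputs from the article: 487 recruited; 194 per group; 20% dropout allowed; target 485. The planning figure reproduces: 2 × 194 = 388, and 388 / 0.80 = 485. This is context only, since the point does not depend on it.

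The rate of non-attendance at 9 months is not given. Assuming 5% to 25%:
- 487 × 0.05 ≈ 24 without a CTQ, leaving about 463
- 487 × 0.25 ≈ 122 without a CTQ, leaving about 365

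These are not all extra losses. The model's outcome needs a 21-month PANSS, so people without one are excluded anyway. If 80% have it, 487 × 0.80 ≈ 390. If a further fraction m of those lack the CTQ, the complete-case number is 390 × (1 − m):
- m = 0: about 390
- m = 5%: about 370
- m = 10%: about 351
- m = 20%: about 312

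Both the 80% and m are assumptions, and so is complete-case fitting.

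**3. What arm-dependent reporting would do**

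Let T be the arm (0 or 1), X the true trauma score and X* the reported one, with Y = a + bT + cX + dTX.

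*Constant shift in the therapy arm:* X* = X + δT. Substituting X = X* − δT and using T² = T:
- coefficient of T: b − (c + d)δ
- slope of X*: c
- interaction: d, unchanged

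A uniform shift therefore moves the treatment coefficient but leaves a linear interaction alone.

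*Shift that depends on true history:* X* = X + (δ₀ + δ₁X)T. In the therapy arm the slope on X* becomes (c + d)/(1 + δ₁), so the fitted interaction is (c + d)/(1 + δ₁) − c. With d = 0 this equals −cδ₁/(1 + δ₁), which is not zero. A spurious interaction is thus possible, but only if reporting changes unevenly with history.

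The article gives no value for δ, δ₀, δ₁ or c, so none of these terms can be sized from it.

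**The case against.** The strongest reply is that childhood abuse and neglect are fixed long before randomisation, so a retrospective instrument measures the same history whenever it is given. That is right about the construct. It does not cover the recorded score, which is taken after therapy and only in those assessed. The accurate statement is that trauma was not measured at baseline, not that it is not a baseline factor.

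A second reply is that the analysis is exploratory and that its details belong in the analysis plan, which is not shown. Exploratory status does lower the severity. Handling of missing covariates may well be settled in that plan. The mismatch itself, however, lies wholly within the article, which states both the timing and the covariate list. The schedule figure was not available, but the text is explicit.

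Three stronger readings are tempting and are not supported:

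- *That the trial's treatment effect is biased.* The primary model adjusts for baseline PANSS, sex and age with a random effect for site. The CTQ plays no part. One can assume a 0.1 to 0.3 SD arm shift and a slope of 0.2 to get 0.02 to 0.06 SD, but neither input comes from the article. Setting the result against the planned effect of 0.33 would wrongly suggest that the primary comparison is at risk.
- *That a trauma-by-treatment finding would be an artefact.* A uniform shift leaves a linear interaction unchanged. Uneven reporting could distort it, but nothing in the article shows that this occurs. The Interventions section does not describe trauma work.
- *That everyone missing at 9 months is lost because of the CTQ.* Those who also lack a 21-month PANSS are already out.

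**Conclusion.** The inconsistency stands. As written, a measurement taken at the end of treatment and dependent on attendance enters a model described as using baseline information. The problem is confined to the exploratory predictor and subgroup model.

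Its size is open. The extra sample loss is the number of people with a 21-month PANSS but no CTQ, which the article does not give. The range of about 390 down to 312 rests on the assumed 80% retention, 0% to 20% further missing CTQ, and complete-case fitting. Whether reported trauma differs by arm is a reasonable worry, not an established fact, and no bias figure can be derived. The point merits correction before the outcome analysis but falls short of a must-fix.

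**What to change.** 1. Fit the main baseline predictor and moderator model without the CTQ, so that its description as baseline-only is true.
2. Report CTQ completion and CTQ scores by arm.
3. Add the CTQ in a separate exploratory or sensitivity analysis, labelled as measured after randomisation. State the number of participants it uses and how missing CTQ is handled. The article's centre-mean rule is written for data missing at baseline in primary and secondary outcome models and does not clearly cover this variable.
4. Interpret any CTQ result cautiously if completion or scores differ by arm.

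Recruitment closed in May 2015, so a baseline CTQ can no longer be obtained and the remedy has to lie in the analysis. The cost is a change of wording and a little extra analysis. The downside is that trauma history becomes a secondary exploratory question and leaves the main model.

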### Participant change of status

If a participant express that they are unsure whether they wish to remain in therapy, data collection or both, then they are provided with a range of options (reduced number of assessment measures, change in time and venue of their appointments, taking a break from therapy or delaying assessments) to ensure they have been provided with a flexible range of choices. If a participant wish to withdraw from therapy, data collection or both they can do so at any point without having to provide a reason. However, participants are offered the option of providing a reason for withdrawal if they wish to do so. Participants are also offered the choice to complete the self-report measure of potential adverse effects from the trial and return it to the trial manager in a pre-paid envelope.

### Safety monitoring and reporting

We record all events which meet National Research Ethics Committee (NREC) criteria for a serious adverse event (SAE), i.e. any untoward occurrence that: results in death, is life threatening, results in self-harm, results in harm to others, requires hospitalisation or prolongation hospitalisation, results in persistent or significant disability or incapacity, consists of a congenital anomaly or birth defect, or is otherwise considered medically significant by the investigator. In line with NREC guidance, a SAE occurring to a research participant is reported to the main REC where in the opinion of the Chief Investigator the event is related (i.e. resulted from any of the research procedures) and unexpected. To minimise the risk of bias in the appraisal of whether the event is related and unexpected, we seek an independent opinion for each event from a representative of the IDMC, who is an expert clinician in the area of psychosis. The IDMC and ITSC provide oversight of the adverse events and monitor for any patterns in events between the CBT plus TAU and TAU Alone arms of the trial.

In addition to the above, potential unwanted effects of trial participation will be reported as a PANSS 25 % or more deterioration, scores of six or more on the GCI-Improvement Scale and the adverse effects of trial participation self-report measure.

### Statistical analysis

Statistical analysis will take place after full recruitment and follow-up (i.e. there will be no interim analyses for efficacy, although an independent Data Monitoring Committee monitors trial progress and specifically any safety issues on a regular basis). The results of the trial will be presented following the standard CONSORT recommendations. Baseline and follow-up data will be summarised using the appropriate descriptive statistics and graphical summaries. Treatment effects will be presented with 95 % confidence intervals (CI). There will be no adjustment to secondary outcomes CIs for multiple testing. The primary outcome (PANSS total score at 21 months) will be analysed using a linear model that adjusts for pre-specified baseline covariates (baseline PANSS, sex, age) and includes a random effect for site. The development of treatment effects over time will be explored using a repeated measures mixed effects model that makes use of all available data, this assumes missing at random conditional on the observed covariates. The primary analysis will be intention-to-treat on available data (i.e. analyse as randomised). Secondary outcomes will be analysed in a similar way with generalised linear models appropriate for the distribution of the outcome.

We will try to identify subgroups for which the treatment effect is greatest using a prognostic risk model using baseline information. Response to treatment as measured by change in PANSS from baseline to 21 months will be explored in a general linear model. Covariates will include age; sex; baseline secondary outcome measures; childhood trauma; beliefs about self and others; working memory performance; and treatment allocated. Outcome analyses will be repeated excluding participants where the blind was broken to determine the robustness of the findings.

We will also address the influence of compliance and the therapeutic alliance between therapist and participant via causal or ‘mediation’ models. Traditional approaches to mediation [54] assume that confounding between the putative mediator and clinical outcome is absent (i.e. there is no omitted variable bias). We will compare the results of three sets of assumptions: (a) no confounding, (b) that we have measured and are able to adjust for all important confounders [55], and (c) that we are able to effectively adjust for unmeasured confounders (hidden confounding) using instrumental variable-based methods, specifically analyses based on principal stratification [56].

The sensitivities of all treatment effect estimates to missing outcome data will be explored; these models will explore the robustness of the treatment estimates to whatever small amount of missing data there is. The following strategy will be followed: firstly, the main analysis will use all available data that we believe are valid under the assumption of missing at random; secondly, a suite of sensitivity analysis to explore the robustness of the primary analysis to departures from assumptions that includes all randomised participants; finally, if required, sensitivity analyses will include multiple imputation, and imputing a range of values for missing data under missing not at random assumptions [57].

Data missing at baseline will be reported as such. If required for models for primary or secondary outcomes, continuous data will be imputed with the centre specific mean of that variable, missing binary/categorical data will include a missing indicator.

A copy of the intention to treat statistical analysis plan can be found here: http://w3.abdn.ac.uk/hsru/CHaRT/public/content/ShowPage.aspx?page=statistical-analysis-plans.

The economic analysis will estimate the costs of health and social care and quality adjusted life years (QALYs) from a broad societal perspective. This will include NHS secondary and primary care services, formal, independent and voluntary social care services and patients and family expenditure. The key determinants of total direct costs are expected to be those associated with the use of NHS hospital inpatient, outpatient and clinical services provided for the initial trial interventions and associated follow-up. These items comprised approximately 90 % of the total costs for participants in the recent CUtLASS trial who were randomised to second generation antipsychotics [32]. The time horizon for the economic analysis will be the 21 months from recruitment to end of scheduled follow-up. Quality adjusted life years will be the measure of health benefit from the primary analysis. Changes on key clinical measures from baseline to follow-up will be used in sensitivity analyses. QALYs will be measured using the EQ-5D health status measure and associated utility tariffs. Missing cost and QALY data will be treated as described above. Covariates for the cost effectiveness analyses will be identified from previous trials and descriptive analysis of the pooled baseline data.

Dissemination will occur via a number of methods which include publication of trial papers, conference presentations, book chapters, the Psychosis Research Unit website www.psychosisresearch.com and the HTA final report (monograph and trials directory). All authors must have contributed to one of each of the following: the design (conception and design or, acquisition of data and/or analysis and interpretation of data), the manuscript (drafting of the manuscript and/or critical revision of the manuscript for important intellectual content) and practical issues (statistical expertise, or obtaining funding, or administrative, technical, or material support, or supervision, or no additional contributions or other practical issues).

Participants will be informed of the results by being offered written and/or face-to-face feedback. This will be led by two co-applicants who are user-led researchers and members of the Psychosis Research Unit (PRU) Service User Research Group (SURG) have agreed to contribute to the process of communicating study findings, such as helping to generate a user-friendly sheet summarising the findings.

We intend to make data available to the scientific community with as few restrictions as feasible, while retaining exclusive use until the publication of major outputs has been completed.

